#### Usual care group 

Participants allocated to the usual care arm (patients and carers) will receive at enrolment, information about support, including recommendations to use services, such as Pancare Foundation and the Cancer Council telephone support line (both staffed by cancer nurses). At the end of the data collection period (6-months post enrolment), participants in the usual care arm will be offered access to *iCare* for their ongoing use.

#### Intervention group

Participants (patients and carers) allocated to the intervention arm will be automatically redirected to *iCare*’s main menu page after completing the enrolment questionnaire. This will allow for seamless entry into the program. Participants will also be sent an email with a link to the *iCare* program, a user identification number and instructions for how to download the program to their preferred device (ie, smartphone, tablet, laptop etc.) for future use. Video instructions on how to use *iCare* will be provided. Automatic email notifications will be sent weekly highlighting information and resources within *iCare*. Participants will be able to access *iCare* as needed (i.e., no frequency/module release/duration limits), allowing for observation of natural use. Participants will have continued access to *iCare* following completion of the study.

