#### Social media and clinical recruitment

Recruitment will be monitored weekly; if UGICR recruitment does not generate sufficient participation levels within 18 months, recruitment of patients and carers will be supplemented by:i.social media: advertisements via Meta (Facebook and Instagram) will include a brief description of the study e.g., ‘If you would like to try a web-program for people living with upper GI cancer or their carers, click here’. A link on the Meta advertisement will direct those interested to the iCare homepage for full study information; andii.participating health services’ oncologists or surgeons involved in the project. The clinician at participating sites will screen patients at outpatient clinical appointments and provide patients and carers with a flyer highlighting the details of the study and contact information of the project manager.

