#### Feasibility and acceptability of *iCare* (Aim 1)

Feasibility will be measured by: eligibility, recruitment, and retention rates over the 6-month study period. Acceptability will be measured by usage data (e.g. usage patterns, number and length of log-ins, pages viewed, use of interactive features including symptom tracking calendars, the number of external websites accessed via links in the program and number of days between first and last log-in), iCare usage [35] for both patients and carers. Data tracking is embedded within *iCare;* this will be summarised to determine engagement. Satisfaction with the program will also be collected from open ended questions (T2) for the intervention group.

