#### Process evaluation (Aim 5)

The RE-AIM Framework will guide an evaluation of the uptake of *iCare*. Following RE-AIM, data captured through the RCT will assess: Reach [R] – Demographic characteristics of participants will be captured to enable a description and comparison of the sample as a sub-set of the target population. Effectiveness [E] assessed on QoL, unmet needs, carer burden and cost-effectiveness through the RCT. Adoption [A] – from RCT: use of *iCare* over the 3-month intervention period. Surveys will be conducted with participants regarding acceptability and feasibility of *iCare*; perceived barriers and facilitators of use; and the degree to which *iCare* addressed their needs. Google Analytics data will evaluate participants’ *iCare* activity, including login date/times, navigation patterns, page views and duration, and features used (video, audio, and document downloads). Implementation [I]. Fidelity and consistency of delivery will be measured. Maintenance [M] - Additional surveys will elicit perceptions of the potential sustainability of *iCare* from representative clinician and health service multi-disciplinary teams (*n* = 10), Government representatives (*n* = 5), consumers (*n* = 5) and community partners (*n* = 5).

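### The enrolment flow gives every intervention participant a first iCare visit, and the acceptability measures do not separate it from visits the participant chose to make

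*Protocol article*

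**What the plan says.** The Intervention group section of the protocol article states that participants "allocated to the intervention arm will be automatically redirected to" iCare's "main menu page after completing the enrolment questionnaire". It gives the purpose: "This will allow for seamless entry into the program". A link and a user identification number are emailed as well, for later access. The same section says that participants may use iCare as needed, without limits, "allowing for observation of natural use". It also describes weekly prompts: "Automatic email notifications will be sent weekly highlighting information and resources within" iCare.

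The Abstract and the Primary aim section make engagement with iCare the acceptability part of the primary outcome. The Feasibility and acceptability section (Aim 1) lists the measures, among them "number and length of log-ins, pages viewed", use of interactive features, external links followed, and the interval in days from first to last log-in. It says that tracking built into iCare supplies these data. The article does not say how the redirected visit is treated.

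**The concern.** The redirected visit comes from the enrolment process, not from a decision to open iCare. The Discussion expects later delivery through stakeholder websites, where presumably no trial questionnaire would lead into the program. Yet the visit falls within the same usage data as later visits that participants chose to make. A weekly email is different: it prompts, but the participant still decides whether to go to the site.

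If the two kinds of visit are pooled, the level of engagement is overstated, and by proportionately more when few people come back. That is the situation an acceptability trial most needs to recognise, because the Sample size section says the results will inform decisions about a Phase III trial.

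**Working it through.** **Inputs.** The Sample size section plans 162 patients and 162 carers, and allocation is 1:1, so 162 / 2 = 81 per arm in each cohort. The article gives no log-in or uptake rate, so there is no figure of its own to reproduce. The rates and means below are assumptions, shown as ranges.

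**Step 1: is the redirected visit likely to be logged?**
- For: it is described as entry into the program, it lands on the main menu, the emailed link and identification number are for later access, and participants have already registered on the iCare website (Consent and screening).
- Against: the identification number arrives separately by email, and the iCare program content section says the patient or carer pathway is identified at login. The redirect might therefore register as a page view without a log-in.

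Logging is likely but not stated. Steps 2 to 4 assume it.

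**Step 2: log-in counts.** Let m be the mean number of self-initiated log-ins per person. The counted mean is m + 1. The overstatement is 1/m, and the redirect's share of all counted log-ins is 1/(m + 1).

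| m (assumed) | counted mean | overstatement | redirect's share |
|---|---|---|---|
| 1 | 2 | 100% | 50% |
| 2 | 3 | 50% | 33% |
| 10 | 11 | 10% | 9% |
| 20 | 21 | 5% | 5% |

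The shift is one per person, so the ranking of participants by log-in count does not change. What is misstated is the level.

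**Step 3: any ever-accessed figure.** The counted rate is 81/81 = 100% per cohort. If the true share who ever open iCare on their own initiative is p, the overstatement is 100% − p.

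| p (assumed) | number of 81 | overstatement |
|---|---|---|
| 30% | about 24 | 70 points |
| 50% | about 41 | 50 points |
| 70% | about 57 | 30 points |
| 90% | about 73 | 10 points |

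**Step 4: interval from first to last log-in.** The redirect fixes the first log-in at enrolment. Someone who chooses to open iCare only once, on day 60, has an interval of 60 − 0 = 60 days with the redirect counted, and 60 − 60 = 0 days without it.

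**Step 5: if it is not logged as a log-in.** The landing could still enter pages viewed and perhaps time spent, by an amount that cannot be derived from the article. Log-in counts and the interval would then be unaffected.

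**The case against.** The strongest reply is that the protocol's own measures already expose poor engagement. A participant who closes the page after the redirect and never returns shows an interval of zero days, about one page, almost no time, no features and no external links. This stands. A reader might infer that the acceptability outcome cannot show low engagement, but most of the listed measures are graded and one landing on a menu does not saturate them.

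A reader might also infer that a primary uptake endpoint is 100% by construction. No such endpoint is defined. Uptake appears as a feedback topic (Program satisfaction) and as the general subject of the process evaluation, where adoption means use over three months. The 100% figure applies only to an ever-accessed summary, should one be reported, and only if the redirect is logged.

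A further inference might be that recruitment traffic contaminates the results, because "A link on the Meta advertisement will direct those interested to the iCare homepage for full study information". The article does not support this. That route opens only if registry recruitment falls short within 18 months, the clicks are voluntary and precede enrolment, and the Aim 1 measures come from tracking within iCare. The web analytics belong to Aim 5 and are described as covering participants: "Google Analytics data will evaluate participants".

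Two milder replies remain. The phrase about natural use describes unrestricted access and does not claim that every visit is unprompted. That is fair, but the pooled data still mix two kinds of visit. And a counting rule may sit in the full protocol or analysis plan, which are not shown. For that reason the point is not that a rule is missing. It is that the article fixes an automatic first entry into a program whose log-ins, pages and time make up a primary outcome.

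**Conclusion.** The point holds in a limited form. The redirect is stated for the whole intervention arm and creates a first visit that the participant did not initiate. If that visit is logged, mean log-ins are overstated by 100%, 50% or 10% at assumed means of 1, 2 or 10 self-initiated log-ins, the log-in interval starts at enrolment for everyone, and an ever-accessed figure would carry no information. With heavy use the distortion is minor.

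The size rests on two things the article does not give: whether the redirect registers as a log-in, and how often participants will return. A flat statement that all 81 in each cohort will have a log-in by design therefore goes further than the text allows. This is a low-cost improvement to how a primary outcome is reported. It does not show that the acceptability result is invalid.

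**What to change.** Add to Aim 1 that the session opened by the enrolment redirect will be reported separately from later, self-initiated sessions. Give log-in counts and the first-to-last interval both with and without that session, and state the number and percentage of patients and of carers who never return after it. If the redirect proves not to be logged, one sentence saying so settles log-ins and interval, and only its contribution to pages and time needs a note.

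The cost is that sentence and a filter on usage data that iCare is already set to record. The intervention, the redirect and the burden on participants are unchanged. The downside is that log-in figures will look less favourable and that genuine use during the first session appears on its own line. It is still shown, so no information is lost.

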### *iCare* program content

*iCare* is a website developed by Research Technology Architects at Deakin University in collaboration with our co-investigators, partners and consumers. Consumer / stakeholder input, research evidence, guidelines and recommendations informed the modules on *iCare* which provide resources for patients and carers. The program comprises two system pathways (patient or carer). The relevant pathway will be identified at login stage. Similar to our previous work [32, 33], the pathways will provide information, support and resources with an additional facility to identify and record pain for each cancer type.

*iCare* is an interactive platform, organised around 15 modules, with versions for people diagnosed with different upper GI or HPB (pancreas, liver, stomach, bile ducts, oesophagus) cancers.

*iCare* provides relevant information in each module through a mix of video, podcasts and written resources (Fig. 2). Each time a patient accesses the program, they provide information on their current physical and emotional needs and an algorithm directs them to relevant information on the website with all information on the website still able to be accessed. The program is fully flexible allowing participants to engage in the modules most relevant to their needs over the 3-month intervention period.

**Fig. 2 Fig2:**
[figure not shown]
Each landing page for the different cancer types includes 18 modules

### Data collection

Information will be collected at enrolment (T1), 3 (T2) and 6 months (T3) post enrolment. All patient and carer participants will be emailed a link to the online questionnaires administered through Qualtrics at T1, T2 and T3. Each questionnaire will take approximately 20 min to complete. Participants who do not complete questionnaires within 2 weeks will be followed up by telephone at each data collection point. Particpants will receive 2 reminder telephone calls, surveys not returned within 4 weeks after each data collection point will be marked as missing.

Demographic data for intervention and usual care groups: (collected at enrolment T1): age, gender, postcode, date of diagnosis, treatment, length of time in the caring role, patient diagnosis and patient treatment (carer), living situation, distance to treating health service, highest level of education, identification with lesbian, gay, bisexual, transgender, queer, intersex, asexual communities and identification as First Nations or Aboriginal and/or Torres Strait Islander people. Both patient and carer groups will complete a Single Item Literacy Screener (SILS) question that identifies whether participants need assistance to read and understand health information [34]. Health literacy will allow us to assess the health literacy levels of study participants and explore the relationship between health literacy and website use.

#### Feasibility and acceptability of *iCare* (Aim 1)

Feasibility will be measured by: eligibility, recruitment, and retention rates over the 6-month study period. Acceptability will be measured by usage data (e.g. usage patterns, number and length of log-ins, pages viewed, use of interactive features including symptom tracking calendars, the number of external websites accessed via links in the program and number of days between first and last log-in), iCare usage [35] for both patients and carers. Data tracking is embedded within *iCare;* this will be summarised to determine engagement. Satisfaction with the program will also be collected from open ended questions (T2) for the intervention group.

#### Patient outcomes (Aim 2)

*Functional Assessment of Cancer Therapy (FACT-G)* [24] is a 27-item questionnaire, designed to measure four domains of quality of life in people living with cancer and valid for all cancer types.

*Supportive Care Needs Survey (SCNS)* [25] is a 34-item instrument that comprises five main themes (psychologic, health system and information, physical and daily living, patient care and support, and sexuality). It will provide information on the potential impact of *iCare* on patient unmet needs.

#### Carer outcomes (Aim 3)

*Zarit Burden Interview-12 (ZBI-12)scale* [26], a short version of the standard ZBI (22 questions), is a reliable and valid measure of carer burden. The ZBI has been used across a variety of cancer types as well as across different stages of disease.

*Partner and Caregiver Supportive Care Needs Survey (SCNS-P&C)* [27] comprises 45 items that can determine carers' unmet needs, prioritise health-care resources, and tailor supportive cancer care services. It includes subscales of psychological, emotional, work, social and information.

*Caregiver Quality of Life Index-Cancer (CQOLC) scale* [28] measures quality of life and provides information about physical, social, emotional and financial wellbeing. It comprises 35 questions, and has been used in technology-based intervention trials [36].

#### Cost effectiveness data (Aim 4)

The Assessment of Quality of Life – four Dimensions (AQoL4D) [37] will be used to capture health-related quality of life scores and calculate quality-adjusted life years (QALYs) for both patient and carers. QALYs are the preferred outcome metric of economic evaluations as they allow practical ‘value-for-money’ judgements to be made. Program use will be recorded over the intervention period and beyond, via both automated website analytics and self-report satisfaction at T2.

Resource use and costs will be measured via self-report. A questionnaire, previously used by our team in other cancer-related studies, will be used to capture patients’ use of general medical resources, including hospital use (emergency department and admissions) welfare, and productivity losses [38].

### Program satisfaction

Participants in the intervention group will be asked to provide feedback about *iCare*. Quantitative and qualitative data will be collected, including open ended questions on participant satisfaction with the program content, uptake of the program, usability, acceptability, and areas for improvement.

### Sample size and power calculation

This Phase II RCT will provide insights into the intervention feasibility and acceptability as well as estimates of efficacy of the iCare intervention on a range of measures to inform decisions about a larger Phase III trial. We plan to recruit a minimum of 162 patients and 162 carers as dyads or as independent participants. We have successfully recruited patients and carers in the past [39]. An average of 830 Upper GI and HPB cancer cases are reported to the UGICR every year (personal correspondence; September 2023). Assuming, on average, 38% (personal correspondence, UGICR; September 2023) will be eligible and assuming a conservative 26% [39] recruitment rate, we expect to recruit ~ 82 patients and carers per year or 164 in each cohort over 24 months. This pragmatic sample size will provide adequate information to report recruitment and attrition rates, study feasibility and acceptability outcomes for both patients and carers. The sample size will allow preliminary estimation of the treatment effects and between and within participant variability for both patient and carer outcomes to inform Phase III trial planning [40]. Assuming 33% attrition at 3 months [25, 39], complete data from 108 patients and 108 carers (54 per arm) would achieve 80% power to detect large standardised mean differences (Cohen’s d) of 0.54. For the main patient outcome, FACT-G [24] these effect sizes correspond to a mean difference of 13 points between groups (standard deviation = 24) [24]. Clinically Meaningful Changes for the FACT-G scale are in the range of 5–6 [40].

### Analysis plan

Results will be presented for patients and carers independently.

#### Aim 1

We will report on recruitment, adherence, retention, accrual, attrition rates, monthly enrolment by upper GI and HPB cancer type (pancreas, liver, stomach, bile ducts and oesophageal) and characteristics of sample, and determination of productive recruitment methods, and survey completion rates. Reasons for attrition will be ascertained from participants/carers and the MORECare Guidelines will be applied to report and manage attrition [41]. We will report measures of engagement and explore, whether usage of the web-based program is associated with better outcomes in both patients and carers after controlling for potential confounders. Responses to the satisfaction questionnaire (open-ended questions) will be analysed using thematic analysis to identify themes and subthemes in the data.

#### Aims 2–3

Preliminary effect size and variance estimates for patient (QoL, unmet needs) and carer (burden, unmet needs, QoL) outcomes will be estimated using linear mixed models. The models will include study arm (*iCare/*usual care), time (T1, T2, T3) and time by arm interaction as fixed effects and patient (or carer) as random effect. Models will include the randomisation stratification factor (cancer type) as a fixed effect. Estimates of effect, variability, and intraclass correlation coefficients will be reported for each outcome alongside 95% confidence intervals.

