### Study design

The design is an Australian based phase II randomised controlled trial (RCT) where people diagnosed with upper GI or HPB cancers and their carers will be recruited and allocated (1:1) to receive *iCare* or usual care during a 3-month period. The time period recognises patients’ complex physiological and psychological needs and carer support needs, with outcomes, measured at enrolment (Time 1), 3 months (Time 2) and 6 months post-enrolment (Time 3, Fig. 1).

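### The Aims 2–3 mixed model leaves the baseline arm difference free and so gives up some precision that the T1 score could supply, without bias

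*Protocol article*

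**What the plan says.** The analysis plan for Aims 2–3 lists study arm, "time (T1, T2, T3) and time by arm interaction as fixed effects and patient (or carer) as random effect". It adds: "Models will include the randomisation stratification factor (cancer type) as a fixed effect". No baseline covariate and no equal-baseline constraint is named. The output is described as follows: "Estimates of effect, variability, and intraclass correlation coefficients will be reported for each outcome alongside 95% confidence intervals".

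On timing, the Data collection section states: "Information will be collected at enrolment (T1), 3 (T2) and 6 months (T3) post enrolment". Under Consent and screening, participants learn their group by email after they complete the enrolment questionnaire. Under Randomisation, the first dyad member or a single participant is randomised, and a second dyad member takes the arm already assigned to the first.

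The sample size section gives the scale: "We plan to recruit a minimum of 162 patients and 162 carers as dyads or as independent participants". With 33% lost by the 3-month visit, it states that "complete data from 108 patients and 108 carers (54 per arm) would achieve 80% power to detect large standardised mean differences (Cohen’s d) of 0.54". On the FACT-G scale this is said to "correspond to a mean difference of 13 points between groups (standard deviation = 24"). The same section says that the effect and variability estimates are to inform Phase III planning.

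**The concern.** With T1 as an outcome row and arm, time and their interaction all free, the time-by-arm terms are differences between arms in change from T1. For anyone whose T1 preceded allocation, the expected T1 arm difference is zero. The model spends information on estimating it, and does not use the T1 score to explain later variation between participants as well as baseline adjustment would. The intervals are wider than the data allow.

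The second matter is the within-person structure. A single participant random effect, taken alone, assumes one correlation for every pair of visits. If T1 and T3 are less alike than T1 and T2, one pooled intraclass correlation hides this. Phase III planners would need the separate correlations to size a baseline-adjusted 6-month endpoint.

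**Working it through.** **Inputs from the protocol article.** 162 per cohort, 1:1, so 81 per arm; 33% attrition at 3 months; SD 24; difference 13 points; 95% intervals.

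**Assumptions.** Two-sided 5% level; visit correlation ρ of 0.5 to 0.7; 45% lost by T3. None of these is stated. The T3 loss does not enter the T2 results below.

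**The plan's own figure.** 13/24 = 0.54. 162 × 0.67 ≈ 108, or 54 per arm. Power = Φ(0.54 × √(54/2) − 1.96) = Φ(0.85) ≈ 0.80. The stated power reproduces.

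**Precision at T2.** Let n₁ = 81 and n₂ = 81 × 0.67 = 54.27 per arm, with constant correlation and equal variances.

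- Planned time-by-arm contrast: variance = 24² × 2 × [(1 − ρ²)/n₂ + (1 − ρ)²/n₁]
- Common T1 mean, or T1 as covariate: variance = 24² × 2 × (1 − ρ²)/n₂
- Planned model, arm difference at T2: variance = 24² × 2 × [(1 − ρ²)/n₂ + ρ²/n₁]

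The excess variance of the first over the second is (n₂/n₁)(1 − ρ)/(1 + ρ) = 0.67(1 − ρ)/(1 + ρ).

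| ρ | Planned contrast SE | Baseline-adjusted SE | Excess variance | Excess SE | Planned arm difference SE |
|---|---|---|---|---|---|
| 0.5 | 4.41 | 3.99 | 22% | 11% | 4.41 |
| 0.6 | 3.98 | 3.69 | 17% | 8% | 4.32 |
| 0.7 | 3.48 | 3.29 | 12% | 6% | 4.22 |

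At ρ = 0.6 the 95% half-width falls from 1.96 × 3.98 = 7.8 to 1.96 × 3.69 = 7.2 FACT-G points. The loss equals discarding 1 − 1/1.17 ≈ 14% of the data, about one participant in seven. If the effect is read as the arm difference at T2, the loss is the same at ρ = 0.5 and larger above it. With 44 per arm left at T3, the T3 contrast SE is 5–11% larger for ρ from 0.7 to 0.4.

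**Interval coverage if correlation decays.** Take 54 per arm with complete data and assumed correlations 0.7 (T1–T2), 0.7 (T2–T3) and 0.5 (T1–T3). A random intercept pools these to (0.7 + 0.7 + 0.5)/3 = 0.633.

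- Model SE of either change contrast: 24 × √(4 × 0.367/54) = 3.96
- True SE, T3 change: 24 × √(4 × 0.5/54) = 4.62; coverage 2Φ(1.96 × 3.96/4.62) − 1 ≈ 91%
- True SE, T2 change: 24 × √(4 × 0.3/54) = 3.58; coverage about 97%, so too wide
- Arm difference at T3: model and true SE are both 24 × √(2/54) = 4.62; coverage 95%

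Other assumed patterns, with 81 per arm at T1 and 54 per arm at T2 and T3 (adjacent-visit correlation first, then T1–T3), from generalised least squares:

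| Correlations | T3 change | T3 arm difference | T2 change |
|---|---|---|---|
| 0.5 / 0.25 | 92.0% | 94.4% | 96.4% |
| 0.6 / 0.36 | 91.4% | 94.3% | 96.7% |
| 0.7 / 0.49 | 90.8% | 94.2% | 96.9% |
| 0.6 / 0.5 | 93.3% | 94.7% | 95.8% |
| 0.6 / 0.6 | 95.0% | 95.0% | 95.0% |

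The T3 arm difference falls to about 91–92% only if the variance also rises by T3, which is a further assumption.

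**The case against.** **The planned model is standard and valid.** This stands. The loss is in efficiency. At ρ = 0.6 it is 0.6 points of half-width, and both 7.8 and 7.2 exceed the 5–6 points that the article calls clinically meaningful. The primary outcomes are feasibility and acceptability. What remains is that the T1 score is collected anyway, so the gain costs no data.

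**A journal article need not give the residual covariance.** This also stands. The article names a participant random effect; it does not say that nothing else models the within-person dependence, nor that standard errors are model-based. A separate analysis plan may add both. The coverage point is therefore conditional.

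**A free T1 arm difference suits this design.** This stands in part. A second dyad member may complete T1 after the pair's arm is set and known, so a T1 difference among them need not be chance. That limits a common-baseline constraint. It does not remove the loss for first and single members, and a sensitivity analysis can deal with it.

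**The stronger reading.** A reader might infer that the 6-month intervals are too narrow in general. The documents do not support this. They give no visit correlations, and they do not say whether the reported effect is the change contrast or the arm difference. The shortfall belongs mainly to the T1-to-T3 change contrast under decaying correlation. In the same scenarios the T3 arm difference is close to nominal and the T2 change interval errs in the opposite direction.

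**Conclusion.** The efficiency point holds. As written, the time-by-arm contrast at T2 has a standard error about 6–11% larger than a baseline-adjusted analysis of the same data, at ρ from 0.7 to 0.5 with the protocol's SD and attrition. The direction holds for any correlation below 1 when T1 precedes allocation; the size rests on the assumed ρ. A reader should not infer bias or an invalid analysis.

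The covariance point is secondary. It needs two conditions: the participant effect is the only within-person dependence, and correlation falls with time. Then the T3 change interval covers about 91–93%. With constant correlation and equal variances, coverage is nominal at both visits.

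**What to change.** Model the T2 and T3 scores with arm, time, arm-by-time, cancer type, the T1 score and its interaction with time as fixed effects. A constrained longitudinal model with a common T1 mean and arm effects only at T2 and T3 is an alternative. State that the T2 and T3 arm differences are the reported effects.

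Use an unstructured within-person covariance and report the visit-specific correlations for Phase III. The two changes belong together: with a common T1 mean but still only a random intercept, T3 coverage under the 0.6 / 0.36 pattern is 92.3%.

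Flag second dyad members whose T1 followed allocation, and check in a sensitivity analysis that excluding them does not change the result.

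The cost is revised analysis wording, slightly more analysis work, and six covariance parameters for three visits where a random intercept uses two. No new outcome data are needed; the flag needs only the order of T1 completion and allocation.
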